### Interventions

Patients eligible for participation will be counselled and receive written information. All patients must provide written informed consent prior to participation. After written consent patients will be randomised to either
Nonavalent HPV-vaccine (Gardasil-9®) orPlacebo vaccine (physiological salt solution for injections)

The LEEP should be performed according to guideline for regular care. Preferably, at the day of LEEP the first vaccination should be administered. The first vaccination should be administered at least within 4 weeks after the LEEP. This time window was chosen in particular for logistical reasons, for example with the see and treat method. The second dose should be administered at least one month after the first dose and the third dose should be administered at least 3 months after the second dose. All three doses should be given within a 1-year period. Although studies do not indicate adverse pregnancy outcomes, patients will be asked to use reliable contraceptive during the vaccination period (6 months). Follow-up will be according the Dutch guideline for cervical and vaginal dysplasia (CIN, AIS and VAIN 2015) [25], (see Fig. 1: Flowchart study design). One week after each vaccination, telephonic interview is performed to ask for side effect of the injection.

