### Study objectives and outcome

The primary objective is:

The efficacy of nonavalent HPV vaccination in women with a CIN II-III lesion who underwent a LEEP in preventing recurrent CIN II-III after at 24 months follow-up.

The secondary objectives are:
The recurrence of CIN I-II-III at 6, 12 and 24 months.The effect of HPV vaccination on HPV DNA presence at 6 and 24 months after LEEP.The effect of HPV vaccination on Pap-smear results.Number of LEEP for recurrent CIN.Cost-effectiveness analysis from a societal perspective: intramural and extramural medical costs questionnaire (iMCQ) and productivity cost questionnaire (iPCQ) will be performed at the start of the study, at 2 months and after 24 months.Quality of life will be assessed with quality of life questionnaire: Euroqol 5D-5 L at the start of the study, at 2 months, at 6 months and after 24 months.Side effects and adverse events. One week after each vaccination, a telephonic interview will be performed to ask for side effects after the injection.

The tertiary and long-term objectives are:
Cytology result after 5 years by retrieving HPV-test and Pap smear results from the national database of the population based cervical cancer screening program.Cytology result after 10 years by retrieving HPV-test and Pap smear results from the national database of the population based cervical cancer screening program.Vaccination effect on premature delivery and obstetrical complications by comparing the results to a national database on childbirth data.

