**Fig. 2 Fig2:**
[figure not shown]
Schedule of enrolment, interventions, and assessments VACCIN-study. * Follow up is according to national guideline, when needed cytology, HPV typing or colposcopy is performed and data is collected between 6 and 24 months. ** When result at 24 months is either HPV positive or ≥ PAP2 a colposcopy is performed

1 week follow-up:
Side effects of the injection, Result of LEEP (no CIN, CIN I, II or III) and LEEP margins (clear margins or CIN in margins).

2 months follow up:
Side effects of the injection.QoL (Euroqol 5D-5 L) and societal economical costs questionnaire (iPCQ, adjusted iMCQ).

6 months follow-up:
Cytology results and HPV genotype, QoL (Euroqol 5D-5 L) questionnaire.Side effects of the injection.

24 month follow-up:
Cytology results and HPV genotype. When either test is abnormal, colposcopy will be performed and biopsies taken for histologic study endpoint.QoL and societal economical costs questionnaire (iPCQ, adjusted iMCQ).All other cytology test, colposcopy results, LEEP result and HPV genotype test between appointment 6 months and 24 months follow-up if appropriate.Pregnancy during follow-up with obstetrical outcome.

60 and 120 months follow-up:
Collection of HPV test and Pap smear result via population screening program and sub sequential treatment.Collection of national database on childbirth data on subsequent pregnancies and the following pregnancy outcomes: gestational age, miscarriages, preterm rupture of membranes.

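### A third dose is permitted up to 1 year, but the contraception request runs for a vaccination period stated as 6 months, so a compliant late dose can fall after the request has ended

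*Protocol article*

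**What the plan says.** The timing rules stand together in the Interventions section of the protocol article:

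- Second dose: "The second dose should be administered at least one month after the first dose".
- Third dose: "the third dose should be administered at least 3 months after the second dose".
- Outer limit: "All three doses should be given within a 1-year period".
- Contraception, in the sentence that follows the outer limit: "patients will be asked to use reliable contraceptive during the vaccination period (6 months"). The same sentence opens by noting that studies have not pointed to adverse pregnancy outcomes.

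The two intervals are minimums. No maximum is given apart from the 1-year limit.

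Side effects are covered in two ways. The Interventions section ties collection to the dose: "One week after each vaccination, telephonic interview is performed to ask for side effect of the injection". The secondary objectives repeat this: "One week after each vaccination, a telephonic interview will be performed to ask for side effects after the injection". Separately, the follow-up list under the Fig. 2 caption enters injection side effects at the fixed 1-week, 2-month and 6-month contacts, and not at 24 months.

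**The concern.** Two adjacent sentences give different lengths for what reads as one period. The dosing rules allow the course to run to 1 year; the contraception sentence calls the vaccination period 6 months. A site or participant who follows the printed number would regard the request as finished at month 6, although a dose given later is still within protocol.

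What is at stake is a participant-facing instruction. The Abstract says that CIN is mostly found in women of reproductive age, the randomisation section describes its 30 to 44 stratum in those terms, and pregnant women are excluded at entry. The request is tied to the vaccination period, yet the number attached to it does not span the dosing that the same paragraph permits.

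**Working it through.** **Inputs**, all from the Interventions section: dose 1 to dose 2, at least 1 month; dose 2 to dose 3, at least 3 months; all doses within 1 year (12 months); stated vaccination period, 6 months. I count months from the first dose, because the article does not name a starting point for either the 1-year limit or the 6 months.

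**Can the stated 6 months be reproduced from the dosing rules?**

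- Earliest compliant third dose = 0 + 1 + 3 = month 4.
- Latest compliant third dose = month 12.

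The permitted course therefore lasts between 4 and 12 months. Six months lies inside that range, but it is neither the minimum nor the maximum and does not follow from any stated limit.

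**Gap.** 12 - 6 = 6 months. A third dose given after month 6 and up to month 12 complies with the dosing rules and falls after the stated contraception period. Since the second interval is also only a minimum, a second dose could fall there too: with dose 3 at month 12, the latest compliant dose 2 is 12 - 3 = month 9.

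**Side effects, set side by side.**

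| Source | Trigger | Covers a dose after month 6? |
|---|---|---|
| Secondary objectives | one week after each vaccination | Yes |
| Interventions | one week after each vaccination | Yes |
| Follow-up list, Fig. 2 caption | fixed contacts at 1 week, 2 months, 6 months | No entry after month 6 |

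The first two rows have no calendar limit, so a dose at month 10, for example, still triggers an interview. The third row fits a course that ends by about month 6.

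**Primary outcome.** The first dose may be given up to 4 weeks after LEEP, so the latest compliant third dose is about 1 + 12 = 13 months after LEEP. The 24-month assessment comes about 24 - 13 = 11 months later. Every permitted dose precedes it.

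**The case against.** The strongest defence is that the contraception request covers the vaccination period, whatever its length, and that the 6 months in parentheses is only the planned course. On that reading the 1-year limit is an allowance for delayed doses, and the request extends with the delay. The fixed side-effect contacts at 1 week, 2 months and 6 months fit such a plan. The flowchart and the schedule figure are not shown and may give planned dose times, and the text is a condensed article. The request is also introduced as a precaution.

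This softens the point but does not remove it. The article never says that 6 months is nominal or that the request follows the actual course. Both figures are printed, so the problem is a conflict in stated text and not detail left to a fuller document.

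Three stronger readings are tempting, and the documents do not support them:

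- A reader might infer from the fixed-contact list that side effects of late doses go uncollected. They do not: two sections require an interview one week after each vaccination. All that remains is a mismatch between that list and the 1-year window.
- A reader might infer that the wide window undermines the 6-month HPV and cytology comparisons. With a third dose due around month 6, the 6-month assessment would still mix women before and after that dose, so the discrepancy is not the cause. Both blinded arms follow the same rules, so the randomised comparison is not biased.
- A reader might take the exclusion of pregnant women as proof that the two periods were meant to coincide. It is an entry criterion and does not fix the length of contraception. It only shows why the conflict deserves attention.

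**Conclusion.** The point holds as an internal conflict in the Interventions section. The dosing rules allow a third dose from month 4 to month 12, while the contraception request is attached to a period of 6 months; up to 6 of the 12 permitted months are left over.

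That is a calendar range, not a count of women. The documents give no figure for how many would be dosed after month 6, and no harm is claimed. The size of the gap assumes that both periods start at the first dose, and the conflict assumes that the 6 months is read as printed. The point does not touch randomisation, the primary outcome, sample size, alpha or power. It merits correction because it concerns an instruction to participants and is cheap to put right.

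**What to change.** The clinical lead should reconcile the dosing window and the contraception period in the Interventions section so that both refer to the same period with the same starting point, and carry the agreed wording into the patient information. The fixed-contact list under the Fig. 2 caption should then be aligned with it, for instance by stating that injection side effects are recorded at the one-week interview after each dose. This review does not say which period is right. No new side-effect procedure is needed, since collection is already tied to each dose.

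The cost is a short protocol amendment and a matching change to the patient-information text, with no recalculation and no change to the analysis.

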**Fig. 1 Fig1:**
[figure not shown]
Flowchart study design follow-up

### Sample size calculations

The sample size calculations have been based on the only publication available at the time of preparing this trial. This retrospective cohort study describes an incidence of 2.5% in women treated with quadrivalent HPV vaccine, against 8.5% in the untreated group (Kang et al., 2013). With a target power of 0.8 and an alpha of 0.050, a total number of 646 patients needs to be recruited into the study if the incidence of CIN II-III at two-year follow-up is 3% in the group receiving active treatment, and 8% in the group receiving placebo. Clinical practice shows that the proportion of women who do not attend follow-up visits in this population is high. Therefore, a loss to follow-up is anticipated of 10 to 15%. To compensate for such attrition, the total number of patients that is to be recruited for the study is rounded to 750 patients in total.

### Data collection

All data will be collected using an eCRF and by means of electronic questionnaires. The eCRF and questionnaire data will be collected and stored using Castor EDC, which is also used for randomisation. Subject numbers will be assigned sequentially to subjects enrolled in the study. Stored data is only accessible to the principal and coordinating investigator.

The following data and outcome parameters are collected (see also Fig. 2):
Patient characteristics; age, obstetrical history, contraceptive use, condom use complementary to contraceptive, HPV related history, smoking, family planning.Indication for testing, cytology results, KOPAC-classification, HPV genotype, biopsy result.Quality of life questionnaire (Euroqol 5D-5 L) and societal economical costs questionnaire (iPCQ, adjusted iMCQ).Initial Pap smear and HPV test results

**Fig. 2 Fig2:**
[figure not shown]
Schedule of enrolment, interventions, and assessments VACCIN-study. * Follow up is according to national guideline, when needed cytology, HPV typing or colposcopy is performed and data is collected between 6 and 24 months. ** When result at 24 months is either HPV positive or ≥ PAP2 a colposcopy is performed

1 week follow-up:
Side effects of the injection, Result of LEEP (no CIN, CIN I, II or III) and LEEP margins (clear margins or CIN in margins).

2 months follow up:
Side effects of the injection.QoL (Euroqol 5D-5 L) and societal economical costs questionnaire (iPCQ, adjusted iMCQ).

6 months follow-up:
Cytology results and HPV genotype, QoL (Euroqol 5D-5 L) questionnaire.Side effects of the injection.

24 month follow-up:
Cytology results and HPV genotype. When either test is abnormal, colposcopy will be performed and biopsies taken for histologic study endpoint.QoL and societal economical costs questionnaire (iPCQ, adjusted iMCQ).All other cytology test, colposcopy results, LEEP result and HPV genotype test between appointment 6 months and 24 months follow-up if appropriate.Pregnancy during follow-up with obstetrical outcome.

60 and 120 months follow-up:
Collection of HPV test and Pap smear result via population screening program and sub sequential treatment.Collection of national database on childbirth data on subsequent pregnancies and the following pregnancy outcomes: gestational age, miscarriages, preterm rupture of membranes.

### Statistical analysis

The main analysis for the primary outcome testing the hypothesis of superiority of nonavalent vaccine as compared to placebo, for preventing CIN II-III recurrence after 24 months will be conducted using a χ^2^ test. Outcome measure for the primary outcome is a relative risk with 95% confidence interval.

Relative risks will also be estimated for secondary categorical outcomes, with 95% confidence intervals and χ^2^ or Fisher’s exact test for significance. Continuous data will be described using means with standard deviation, or medians with interquartile ranges; t-tests or Mann-Whitney U tests will be used as appropriate. Kaplan-Meier curves will be made for time between LEEP, vaccination with active or placebo and CIN II-III recurrence. The curves will be compared using the log-rank test. Quality of Life will be measured at every visit. They will be assessed with Euroqol 5D-5 L questionnaire. Patients from both groups will be analyzed using generalized linear mixed models.

The cost-effectiveness will be assessed by calculating the incremental cost-effectiveness ratio (ICER), defined as the difference in costs, divided by the average change in effectiveness of the vaccine versus a placebo following LEEP treatment. A Budget impact analysis (BIA) will be performed, in accordance with the principles for good practice for BIA, to address the financial stream of consequences in order to assess the affordability of offering the vaccine following LEEP treatment. BIA will compare the likely impact of replacing LEEP by HPV vaccination on national health plan budgets, on hospital level and on assurance level. From the viewpoint of the government, the broad societal perspective and the ‘budgetary framework for care’ will be highlighted. A valid framework (Markov model) will give insight into the budget consequences. We will also perform sensitivity analyses and a ‘most optimistic versus pessimistic’ scenario. If the vaccine has a preventive effect, it will be included in the new national guideline. As a result, the health care insurance can compensate this as regular care.

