**Discussion:**

Although prophylactic HPV vaccines are highly effective, little is known about the effectivity of HPV vaccines on women with CIN. Multiple LEEP treatments are associated with complications. We would like to evaluate the efficacy of HPV vaccination in addition to LEEP treatment to prevent residual or recurrent cervical dysplasia and decrease risks of repeated surgical treatment.

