### In- and exclusion criteria

Women are eligible for participation if they are eighteen years old or above, histologically proven CIN II or III and will be treated with a LEEP. Inclusion must be within four weeks after LEEP. Exclusion criteria are: a prior HPV vaccination, invasive carcinoma, immune-compromised women, pregnant women, prior treatment for CIN-lesions, insufficient understanding of the Dutch language or allergic to vaccine components.

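### The budget impact analysis is defined as vaccination replacing LEEP, which contradicts the add-on design, the sentence before it and the ICER contrast

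*Protocol article*

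**What the plan says.** The economic paragraph of the Statistical analysis section contains three statements about what is compared.

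- The ICER is a difference in costs "divided by the average change in effectiveness of the vaccine versus a placebo following LEEP treatment".
- The BIA is introduced as a way "to assess the affordability of offering the vaccine following LEEP treatment".
- The next sentence defines the BIA comparison: "BIA will compare the likely impact of replacing LEEP by HPV vaccination on national health plan budgets". It adds the hospital and insurer levels.

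Elsewhere the design is plainly add-on. Under In- and exclusion criteria, women qualify if they have "histologically proven CIN II or III and will be treated with a LEEP". The Interventions section places the first injection on the day of the LEEP or within four weeks after it. The Discussion part of the Abstract states the aim: "We would like to evaluate the efficacy of HPV vaccination in addition to LEEP treatment". Among the secondary objectives, the LEEP outcome is "Number of LEEP for recurrent CIN", that is, repeat procedures.

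**The concern.** A budget impact analysis depends on which two policies it sets against each other. The only sentence that defines this one names a policy in which vaccination is given instead of LEEP. The randomised contrast is LEEP plus vaccine against LEEP plus placebo, so it says nothing about recurrence or cost in women who are vaccinated and not excised.

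As written, the ICER and the BIA also have different comparators. The Markov model that is to show the budget consequences then has no single defined one.

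The stake is the use made of the result. The BIA addresses government, hospital and insurer budgets, and the same paragraph links a preventive effect to guideline inclusion and reimbursement. If index LEEPs were credited as saved, the saving shown to those readers would be one the trial cannot support.

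**Working it through.** **The plan's own figure.** The article gives no figure for the BIA. The rates used below come from Sample size calculations, so that calculation was reproduced first. With 3% v 8%, two-sided alpha 0.05 (sidedness is not stated), power 0.80, 1:1 allocation and unpooled variance:

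n per arm = (1.960 + 0.842)² × (0.08 × 0.92 + 0.03 × 0.97) / 0.05² = 322.4, rounded up to 323, or 646 in total.

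This matches the stated 646, so 3% v 8% is indeed the design assumption.

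**Which comparison each statement implies.**

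| Place | Index LEEP with vaccine | Index LEEP in comparator |
|---|---|---|
| Eligibility and Interventions | yes | yes |
| ICER definition | yes | yes |
| BIA purpose sentence | yes | not stated |
| BIA comparison sentence, read literally | no | yes |

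Only the last row departs from the design.

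**Size of the departure, in procedures.** Take 1000 women and assume one repeat LEEP per recurrence.

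- LEEP alone: 1000 × (1 + 0.08) = 1080.
- LEEP plus vaccine: 1000 × (1 + 0.03) = 1030.
- Avoided by adding vaccine: 1080 − 1030 = 50, which is 50 / 1080 = 4.6% of all LEEPs.
- Index LEEPs credited as saved under literal replacement: 1000.
- Ratio: 1000 / 50 = 20.

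**Range over the recurrence rates in the article.**

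| Rates, vaccine v no vaccine | Source | LEEPs avoided per 1000 | Ratio |
|---|---|---|---|
| 3% v 8% | Sample size calculations | 50 | 20 |
| 2.5% v 8.5% | Background, vaccine HPV types | 60 | 17 |
| 2.5% (9/360) v 7.2% (27/377) | Background, any HPV type | 47 | 21 |
| 6.4% v 17% | Background upper figure, with the design relative risk 3/8 assumed | 106 | 9 |

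Last row: 0.17 × 3/8 = 0.06375; 170 − 63.75 = 106.25; 1000 / 106.25 = 9.4.

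These are counts of procedures. The article gives no unit cost for vaccine, LEEP or follow-up, so they cannot be turned into money.

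**The case against.** The strongest reply is that the surrounding text already settles the comparison. The sentence before concerns vaccine given after LEEP, the ICER does too, and the LEEP outcome counts repeat procedures. On that view the sentence is loose wording for replacing repeat LEEPs. A BIA built from the trial contrast could not remove index LEEPs anyway, because no arm supplies the data. This reading is plausible, and it is a good reason not to assume that the model will be run literally. It does not make the sentence right: it is the one that defines the comparison, and nothing in it limits LEEP to repeat or recurrent cases.

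A second reply is that the article condenses a fuller protocol. That excuses missing economic detail, but not a comparator that is stated and then contradicted within the same paragraph.

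A reader might also draw stronger conclusions that the article does not support.

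- *That a cost-adding policy would be made to look cost-saving, or that the corrected result would be less favourable.* Without unit costs or any projected budget effect, neither the sign nor the change can be shown.
- *That avoided repeat procedures are the only legitimate offset.* The plan takes a societal perspective, collects medical and productivity costs, and follows obstetric outcomes. Downstream consequences of fewer recurrences may count as well.
- *That 50 per 1000 is a ceiling.* It rests on 24-month design rates. The plan also foresees optimistic and pessimistic scenarios, and the article quotes recurrence of up to 17%.

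**Conclusion.** The contradiction stands. The BIA comparison as written is not the one the trial makes, nor the one named in the preceding sentence and in the ICER. Whether it is a slip or an intended scenario cannot be told from the article.

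If it were applied literally, the procedure offset would be overstated about 20-fold at the design rates, and about 9 to 21-fold across the rates quoted. This rests on one repeat LEEP per recurrence and, for the 17% case, on the design relative risk carrying over. The effect on budgets in money is not known.

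The error is confined to the BIA and its model. The primary χ² test, the relative risk, the sample size and the ICER as defined do not depend on it. It should be corrected before the economic analysis is run, but it does not threaten the trial's main conclusion.

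**What to change.** Restate the comparison as: *the BIA compares LEEP plus HPV vaccination with LEEP alone.* Then specify that:

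- the vaccine cost falls on every vaccinated woman;
- no index LEEP is counted as saved;
- offsets come from fewer recurrences and their downstream consequences, within the perspectives the plan already names;
- the Markov model uses the same comparator as the ICER.

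The cost is an edit of a sentence or two in the protocol or economic plan. It needs no new data and no change to the randomised comparison. If a replacement scenario is truly wanted, it should be labelled as a separate exploration that rests on outside inputs and not on this trial.
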